## Abstract

**Background:**

Osteoporosis and vertebral fracture can have a considerable impact on an individual’s quality of life. There is increasing evidence that physiotherapy including manual techniques and exercise interventions may have an important treatment role. This pragmatic randomised controlled trial will investigate the clinical and cost-effectiveness of two different physiotherapy approaches for people with osteoporosis and vertebral fracture, in comparison to usual care.

**Methods/Design:**

Six hundred people with osteoporosis and a clinically diagnosed vertebral fracture will be recruited and randomly allocated to one of three management strategies, usual care (control - A), an exercise-based physiotherapy intervention (B) or a manual therapy-based physiotherapy intervention (C). Those in the usual care arm will receive a single session of education and advice, those in the active treatment arms (B + C) will be offered seven individual physiotherapy sessions over 12 weeks. The trial is designed as a prospective, adaptive single-blinded randomised controlled trial. An interim analysis will be completed and if one intervention is clearly superior the trial will be adapted at this point to continue with just one intervention and the control. The primary outcomes are quality of life measured by the disease specific QUALLEFO 41 and the Timed Loaded Standing test measured at 1 year.

**Discussion:**

There are a variety of different physiotherapy packages used to treat patients with osteoporotic vertebral fracture. At present, the indication for each different therapy is not well defined, and the effectiveness of different modalities is unknown.

**Trial registration:**

Reference number ISRCTN49117867.

## Background

Each year 25,000 people in the UK have vertebral fractures related to their osteoporosis and many are referred for physiotherapy to help them recover after their fracture. Osteoporosis and vertebral fracture can have a considerable impact on an individual’s health-related quality of life (QoL) due to pain, limitations in activity, social participation and altered mood [1,2]. Vertebral fractures are closely related to increased thoracic kyphosis, which, along with a loss of lumbar lordosis, is linked to increased spinal loading and back extensor muscle weakness. This can lead to an increased risk of further fracture [3,4]. Hyperkyphotic posture is also associated with increased back pain and balance disturbance with a subsequent increased risk of falls and fractures as a result of falling [5,6].

Physiotherapy includes a variety of treatment options, such as exercise programmes or ‘hands on’ treatments such as massage and mobilisations. There is increasing evidence that physiotherapy interventions that address pain and physical impairments may have an important role in improving QoL and reducing the fracture risk in people with osteoporotic vertebral fractures. However, we do not know which type of physiotherapy is most helpful, the cost of treatment to the National Health Service (NHS), or what patients think of their treatment.

### Evidence for manual therapies

#### Manual mobilisation

Traditionally, physiotherapists use manual mobilisation in the management of back pain. However, evidence for the effectiveness and safety of manual mobilisations in the management of thoracic hyperkyphosis in elderly people is limited. Some physiotherapy guidelines caution against using spinal mobilisation in individuals with osteoporosis. High velocity spinal manipulation techniques are contraindicated [7] and concerns about the use of low velocity spinal mobilisation techniques have been expressed. However, recent practice surveys, case reports and two randomised controlled trials (RCTs) suggest these techniques can be used safely [8-11]. No serious adverse events were reported in either RCT of low velocity spinal mobilisation. Both RCTs have small sample sizes, short-term follow-up and have tested a combined treatment protocol of exercise and manual therapy including postural taping. These factors make it difficult to draw confident inference about the safety and effectiveness of the various treatment methods [8,9].

#### Postural taping

Postural taping uses tape applied to the skin to provide increased proprioceptive feedback about postural alignment, improve thoracic extension, reduce pain and facilitate postural muscle activity and balance [6,8,9,12].

### Evidence for exercise interventions

A number of systematic reviews and meta-analyses report the positive effects of exercise on bone mineral density (BMD), muscle strength, QoL and falls and fractures in men and women with osteoporosis or low BMD [13-16]. It is known that an osteoporotic vertebral fracture leads to axial posture deformity which can increase both the fear and the actual risk of falling. Strategies to address falling are an important component of any treatment programme for this patient group [5,6,17,18]. A number of RCTs have found that a combined balance and progressive strength training programme produced the best results in terms of maintaining leg strength, balance, BMD and physical function compared to balance or strength training alone [14,19-21].

RCTs of exercise interventions in people with vertebral osteoporosis also report benefits of reduced pain and improved QoL, strength and balance [22-28]. Interventions range from simple back extension exercises to a variety of general weight-bearing exercise, balance activities, stretches and combined upper limb, trunk and lower limb strengthening. The interventions were delivered in a class format [26-28], as a home programme [23,25] or as a combination of physiotherapist-led along with home exercise programmes [28]. There was no evidence that any of these delivery options was superior to another.

Overall, there is some evidence that both manual therapy and exercise interventions can be beneficial for this patient group. A limited number of studies [8-12] provide strong support for the use of manual therapies but these are inadequately powered. There is some higher quality evidence available to support exercise prescription for individuals with osteoporosis but only a few studies examine exercise in osteoporotic populations with vertebral fracture [22,24,28]. Of these, only a small number combine weight-bearing, strength and balance activities and, to date, none have included men. Whether exercise therapy is more effective than manual therapy is not known and further information is needed about the longer term outcomes of either intervention.

### Objectives

This paper describes the trial protocol for a large, pragmatic RCT to assess the effects of a physiotherapy intervention based on exercise or manual therapy compared to usual care for people with osteoporosis and a clinically diagnosed vertebral fracture.

The secondary objectives are: 1) to compare the effects of manual therapy with exercise therapy; 2) to investigate the acceptability and adherence to the physiotherapy programmes for both patients and therapists; 3) to conduct a parallel health economic analysis to assess the cost effectiveness of the different treatment strategies from an NHS, Social Services and patients’ perspective; and 4) to conduct a nested qualitative study to explore the experiences and views of people with osteoporosis and vertebral fracture regarding their treatment, their perceptions regarding the appropriateness and acceptability of the interventions and to explore the factors influencing their adherence to the intervention programmes.

## Methods/Design

### Trial design

The trial will be a prospective, multi-centre assessor-blinded, three-arm RCT with a nested qualitative study and an adaptive design. Patients will be randomised between three arms: usual care (control) group (A), manual therapy (B) and exercise therapy (C). Those in the usual care arm will receive a single session of education and advice, and those in the active treatment arms (B + C) will be offered up to seven individual physiotherapy sessions over 12 weeks. Clinical assessment will be performed at baseline (week 0), 4 months and 12 months, with postal questionnaires about QoL administered at 6 and 9 months. An interim analysis will be conducted once 75 participants are recruited to each arm and have completed their 4 month follow-up. Following this interim analysis the study may be adapted. If both intervention arms are sufficiently promising and sufficiently similar the study will not be adapted and recruitment will continue into both intervention arms. If one arm, manual therapy or exercise therapy, is not sufficiently promising relative to control or sufficiently similar to the other intervention arm, this arm will be dropped from the study and the study will be adapted to continue as a two arm RCT with participants randomised between the control and remaining intervention arm. If neither arm is sufficiently superior to the usual care arm the trial will be stopped.

The protocol conforms to CONSORT guidelines for non-pharmacological studies [29] (Figure 1).

**Figure 1 F1:**
[figure not shown]
Study flow chart.

### Ethics approval

The study protocol was approved by South Central Research Ethics Committee [Reference 12/SC/0411]. Oxford University is the sponsor. The trial is registered with the International Standard Randomised Controlled Trials database ISRCTN reference number 49117867.

### Trial status

Recruitment started in **November 2013**.

### Participants

Six hundred patients will be recruited from 10 or more centres across the UK. Men and women with osteoporosis who have had a least one symptomatic vertebral fracture will be eligible for inclusion if they meet the following criteria.

### Inclusion criteria

1. Willing and able to give informed consent for participation in the study.

2. Diagnosis of primary osteoporosis confirmed by radiograph or DEXA scan (−2.5 SD below young adult mean) at lowest lumbar level.

3. At least one previous vertebral fracture.

4. Men and women aged 18 years or older.

5. Female participants to be postmenopausal; that is, no period in the last 2 years.

6. All should be able to walk at least 10 metres independently with or without an aid and be able to understand and participate in a physiotherapy programme.

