### Secondary outcomes

There are a number of outcomes included seeking to assess a number of different aspects of symptoms, function and activity. We will be piloting the package, and if the burden of measurement is too great, some measures will be dropped and the protocol amended.

The Functional Co-morbidities Index will be completed as other diseases are likely to be present in this older population which might affect physical outcomes [33].

Spinal curvature and flexed posture will be described by recording height (cm) and thoracic kyphosis. Thoracic kyphosis will be measured using a flexicurve ruler with the patient in a standing position to calculate an index and angle of kyphosis [34].

Other outcomes include measures of balance, mobility and physical activity. Each test is reliable and valid, has been used with older, community dwelling adults and shown to be responsive in previous rehabilitation studies.

•The Short Performance Physical Battery will be used to assess lower extremity physical function [35]. Poor performance is predictive of future disability, hospitalisation and care needs.

•The Functional Reach Test will be used to specifically evaluate standing balance and to act as a predictor of falls risk [36].

•A 6 minute walk at self-selected speed over a 30 metre course will be used to measure exercise endurance; an important parameter of functional, community mobility [37].

•The Physical Activity Scale for the Elderly is a short, self-administered questionnaire to assess activity in the past week [38].

•The EuroQol EQ-5D-5 L is a short, generic measure of QoL and will be completed to facilitate the assessment of cost-effectiveness and also to give a comparison with other clinical conditions [39].

•Participants will be asked to specifically rate back pain on activity and at rest using a 10 point visual analogue scale.

•Information about fractures and falls will be collected using a standardised definition and a prospective participant completed event calendar. These will be mailed to participants monthly during the year of the study and participants will be telephoned by the trial co-ordinator to promote adherence and to check this information is captured precisely [40].

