### Qualitative study

The qualitative study will help to provide a picture of the issues facing participants with osteoporosis and vertebral fracture who participate in the treatment interventions arms of the study. Semi-structured interviews will be conducted by a researcher experienced in the design, collection and analysis of qualitative data. Specific topics covered will be exercising with osteoporosis (including adherence issues), and participant experience of the PROVE trial. We will interview enough participants to ensure we are confident that theoretical sufficiency will be achieved [42]. Purposive sampling will be used to achieve a sample which includes female and male patients, thoracic and lumbar single/multiple vertebral fracture patients and patients of varying activity levels. Fracture site, number of fractures and activity levels are known to influence outcome and, since the majority of research regarding osteoporotic patients’ QoL has previously been undertaken with women, it is considered important to capture the views of male participants within the current study.

Interviews will be conducted either in the hospital or participants homes following the completion of the intervention and the 4-month follow-up appointment. The development of the interview schedule will be iterative and the questions asked may develop and change as the interviews are conducted and analysed [43]. All interviews will be digitally recorded and fully transcribed for analysis. Analysis will utilise Smith’s experiential approach of Interpretative Phenomenological Analysis. A feature of Interpretative Phenomenological Analysis is that the first steps of analysis begin early in the research process with initial data coding and is simultaneous to data collection. Initial analysis of each interview will be carried out as soon after its completion as possible following the guidelines set out by Smith [43].

One in five of the interviews will be coded independently by a second member of the research team with experience of qualitative research to provide a different perspective on the coding. The research team will discuss the development of themes as the research progresses, once again with the aim of providing a different perspective and enhancing the development of themes.

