#### Sample size

The initial sample size calculation is based on a traditional approach to a three-arm trial. We wish to detect a standardised effect of 0.4 in the QUALEFFO; at 80% power and an alpha of 0.05 we would require 180 to 200 participants in each arm or 540 to 600 people (we will use 600 people as the upper limit).

A simulation study was conducted to estimate the power of the study assuming the interim decision rules above were used. The sample size for the interim analysis was chosen to be 75 per arm. This ensures that the power is high while the probability of continuing with an ineffective treatment is sufficiently low. If the true (unknown) treatment effect for an intervention is equal to the control, the probability of dropping that intervention at the interim analysis is approximately 73%. If neither intervention is truly superior to the control, the probability of stopping the entire study at the interim analysis is approximately 60%. Based on this interim analysis sample size the standard error of the estimated difference between the intervention arms and the control arm at the interim analysis will be 0.82.

In the adaptive design of the type proposed, the power of the study may be defined as the probability, given a truly effective intervention, that the intervention remains in the trial at the interim analysis and leads to a significant result in comparison to the control in the final analysis. The specified sample size gives 94% power if the better of the two intervention arms has a true standardised treatment effect of 0.4.

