### Statistical analysis

We will report according to CONSORT standards.

Regression models will be used to estimate the treatment effects (with 95% confidence intervals) and will be adjusted for important covariates (prior fracture history and age). The final statistical analysis will include data from patients from the control arm and intervention arm(s) continuing beyond the interim analysis from both the first and second stages of the trial. The analysis needs to allow for the adaptation made at the interim analysis in order to ensure that the probability of a type I error (false positive result) is controlled. It is proposed to use the analysis method described by Bretz and colleagues [44], applying a Dunnett correction to the comparisons between the intervention arms and the control arm at the first stage and at the second stage unless an intervention arm is dropped.

Complier-average causal effect will be estimated to assess the impact of adherence on the effect of the interventions.

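### The final models leave out baseline activity level, which the article calls an influence on outcome and already measures at week 0; adding it is an optional, small gain in precision

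*Protocol article*

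**What the plan says.** Four places in the protocol article bear on this.

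- **Statistical analysis.** The regression models for the treatment effects "will be adjusted for important covariates (prior fracture history and age". No wording marks these two as examples, so the list reads as complete.
- **Qualitative study.** In explaining how interviewees will be sampled, the article states as a general fact: "Fracture site, number of fractures and activity levels are known to influence outcome". It expects the trial population to include "thoracic and lumbar single/multiple vertebral fracture patients and patients of varying activity levels".
- **Table 1 (Baseline assessment) and Secondary outcomes.** The activity measure is described thus: "The Physical Activity Scale for the Elderly is a short, self-administered questionnaire to assess activity in the past week". Table 1 schedules it at week 0 and at every later assessment. The Recruitment section places the baseline assessment before the call to the randomisation centre, so the week 0 score is a true pre-randomisation value.
- **Inclusion criteria.** Criterion 3 reads "At least one previous vertebral fracture".

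**The concern.** The article identifies activity level as prognostic, measures it in everyone before allocation, and then names a covariate list without it. Adjusting for a prognostic baseline variable removes the outcome variance that it explains from the error term. Leaving it out makes the confidence intervals for both primary outcomes, QUALEFFO 41 and Timed Loaded Standing, somewhat wider than they need to be. It also leaves any chance imbalance in activity between arms unadjusted.

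What is at stake is efficiency. The validity of the comparison does not depend on it.

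**Working it through.** **Inputs from the article**

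- Target effect (Sample size): "We wish to detect a standardised effect of 0.4 in the QUALEFFO".
- Arm size (Sample size): "at 80% power and an alpha of 0.05 we would require 180 to 200 participants in each arm" and "we will use 600 people as the upper limit". I take 600/3 = 200 per arm, which assumes equal allocation.
- Interim analysis: 75 per arm, with a standard error of 0.82 for an intervention-control difference (Sample size). An arm is dropped if it is not more than 0.5 points better than control, or if it is more than 2 points behind the other intervention (Interim analysis decision rules).
- Stated operating characteristics (Sample size): 94% power, about 73% chance of dropping a null arm, about 60% chance of stopping entirely when neither intervention works.

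**Input not in the article:** r, the partial correlation of baseline activity with the outcome, given the covariates already in the model. I assume 0.1 to 0.3.

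**Step 1: the plan's own figures**

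Implied SD = 0.82/√(2/75) = 5.02 points, so an effect of 0.4 SD is 0.4 × 5.02 = 2.01 points.

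- Chance of dropping a null arm: Φ(0.5/0.82) = 72.9% (stated: about 73%).
- Chance of dropping both null arms (bivariate normal, correlation 0.5): 59.3% (stated: about 60%).
- Power, from 1,000,000 simulated trials with the two interim rules, 125 per arm in stage 2, and an inverse-normal combination with a closed Dunnett test at one-sided 0.025: 94.2% when the other intervention has no effect, and 94.0% to 94.6% when its effect is 1 or 2 points (stated: 94%).

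All three reproduce with an SD of 5.02 and no allowance for activity. The stated power therefore does not rely on the missing covariate.

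**Step 2: what adding activity would do**

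- Standard error multiplier = √(1 − r²)
- 95% half-width at 200 per arm = 1.96 × 5.02 × √(1 − r²) × √(2/200)
- Equivalent arm size = 200/(1 − r²)

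| Assumed r | SE multiplier | Half-width (points) | Equivalent n per arm | Adaptive power |
|---|---|---|---|---|
| 0 (as planned) | 1 | 0.98 | 200 | 94.2% |
| 0.1 | 0.995 | 0.98 | 202 | 94.4% |
| 0.2 | 0.980 | 0.96 | 208 | 95.0% |
| 0.3 | 0.954 | 0.94 | 220 | 95.8% |

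Three cautions apply.

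- The SD of 5.02 comes from the 4-month interim. Using it for 12 months, and treating it as the residual SD before activity is added, are both assumptions.
- The power column applies the smaller residual SD at the interim as well as at the end. If the interim decision uses unadjusted mean changes and only the final model is adjusted, the power gain is smaller still.
- The article gives no SD for Timed Loaded Standing. Only the multiplier carries over to that outcome, and r may differ there.

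**Step 3: does fracture history vary?**

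Criterion 3 fixes a minimum of one vertebral fracture. It does not fix number or site. The Qualitative study section expects single and multiple, thoracic and lumbar fractures, and lists site and number beside activity as influences on outcome. The covariate named in the Statistical analysis section can therefore carry two of those three influences. Activity is the one that the named list does not cover.

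**The case against.** The strongest case for leaving the text alone has three parts.

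- The sentence calling activity prognostic was written to justify purposive sampling for interviews. It commits the trial to no model covariate, so nothing is contradicted. That is correct, and it is why this is not an error. The sentence is nevertheless a general statement about outcome, and the authors' belief in it does not depend on the section in which it appears.
- A trial need not adjust for everything it believes prognostic, and the benefit here is unquantified. That also stands. With r = 0.1 the half-width does not change to two decimals, and age and fracture history may already capture part of any raw correlation.
- Chance imbalance is already reflected in an unadjusted confidence interval, and the estimate is unbiased under randomisation. True, so the argument for adding the score is precision alone.

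A reader might infer something stronger: that because every participant has had a vertebral fracture, the fracture covariate is constant and only age is adjusted for. The article does not support this. It would follow only from coding the covariate as vertebral fracture yes or no, which the article nowhere says. How the covariate is coded, and how number and site are recorded, are details that an article commonly leaves to the analysis plan and full protocol, neither of which is shown.

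**Conclusion.** The point holds as an optional improvement. The named covariate list omits baseline activity, which the article itself calls an influence on outcome and collects before randomisation.

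The size rests wholly on an assumed partial correlation. At 0.1 to 0.3, the standard error falls by about 0.5% to 5%, worth about 2 to 20 participants per arm at 200 per arm. On the simulation's assumptions, power moves from 94.2% to between 94.4% and 95.8%.

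A reader might also infer that the trial is underpowered or its estimate biased for want of this covariate. Neither follows: the stated 94% power reproduces without it, and omitting a baseline covariate from a randomised comparison of means does not bias the treatment effect.

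**What to change.** In the Statistical analysis section, add the week 0 Physical Activity Scale for the Elderly score as a pre-specified covariate in the models for both primary outcomes, alongside age and prior fracture history. Specify the week 0 value explicitly, because the scale is repeated after randomisation and later values must not be used for adjustment.

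The cost is one sentence, one degree of freedom per model if the score enters as a linear term, and a simple stated rule for missing baseline scores. No new data are needed. The article reports recruitment as ongoing, allows for later protocol versions, and keeps analysts blinded until the final analysis is complete, so the change can be made before anyone sees results by arm. It should not be made after unblinding.
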